## Abstract

**Background:**

In patients with obstructive jaundice, multi-organ dysfunction may develop.

**Methods/Design:**

This trial is a prospective, open-label, randomized, and controlled study with the objective to evaluate the effect of ursodeoxycholic acid in liver functional restoration in patients with obstructive jaundice after endoscopic treatment. The aim of this study is to evaluate the effect of ursodeoxycholic acid in liver functional restoration of patients with obstructive jaundice after endoscopic treatment. The hypothesis of this trial is that patients with obstructive jaundice, in which will be administered UDCA, in the early phase after endoscopic intervention will have better and faster functional restoration of the liver than patients in the control group.

Patients with obstructive jaundice, randomly, will be divided into two groups: (A) test group in which will be administered ursodeoxycholic acid twenty-four hours after endoscopic procedure and will last fourteen days, and (B) control group.

Serum-testing will include determination of bilirubin, alanine transaminase, aspartate transaminase, gama-glutamil transpeptidase, alkaline phosphatase, albumin, and cholesterol levels. These parameters will be determined one day prior endoscopic procedure, and on the third, fifth, seventh, tenth, twelfth and fourteenth days after endoscopic intervention.

**Discussion:**

This trial is a prospective, open-label, randomized, and controlled study to asses the effect of ursodeoxycholic acid in liver functional restoration of patients with obstructive jaundice in the early phase after endoscopic treatment.

**Trial registration:**

ClinicalTrials.gov, NCT01688375

## Background

The most common causes of obstructive jaundice are choledocholithiasis, strictures of the biliary tract, cholangiocarcinoma, carcinoma of pancreas, and pancreatitis.

First-line serum testing in a patient with obstructive jaundice should include determination of bilirubin (total and direct fractions), aspartate transaminase (AST), alanine transaminase (ALT), gama-glutamil transpeptidase, and alkaline phosphatase levels [1].

In a prolonged obstruction, multi-organ dysfunction including renal failure, cardiac dysfunction, pulmonary dysfunction, poor hepatic metabolism and hemostasis impairment may develop [2].

It is the conventional concept that the high level of serum bilirubin may cause multisystemic damage in patients with obstructive jaundice. Current pathophysiological studies on obstructive jaundice have shown that the damage to the liver, kidney, and immune system of the patients are closely related to endotoxemia. The key event in the pathophysiology of obstructive jaundice- associated complications is endotoxemia of gut origin because of intestinal barriere failure.

Biliary tract obstruction can cause damage to liver cells and Kupffer cell function. In obstructive jaundice hyper secretion of TNF (tumour necrosis factor) by Kupffer cells may support the production of systemic cytokine and be responsible for significant complications [3-5].

Patients with obstructive jaundice frequently suffer haemodynamic and body fluid disturbances. Acute renal failure is a relevant complication in obstructive jaundice. The extra cellular water volume depletion and myocardial dysfunction affects haemodynamic and renal disturbance in patients with obstructive jaundice [6].

Experimental and clinical studies have suggested that a period of at least four to six weeks is needed for the restoration of normal major synthetic and clearance functions of the liver, as well as mucosal intestinal barrier functions [7].

Even though there is a general assumption about the increased bleeding tendency in obstructive jaundiced patients, it was demonstrated tendency for hyper coagulation independent of increased prothrombin times. The most probable cause of this effect is the increased activity of fibrin polymers on platelet membrane [8].

It is important to emphasize that the most patients with obstructive jaundice require appropriate endoscopic and surgical procedures for their treatment [1].

There are a many studies, where ursodeoxycholic acid (UDCA) was administrated in patients with cholestatic liver diseases.

UDCA was discovered, by Hammerstein in 1902, as the principal bile acid in the polar bear [9].

It is used for the dissolution of cholesterol-rich gallstones in patients with functioning gallbladders, and in the treatment of primary biliary cirrhosis [10,11].

Mechanisms underlying the beneficial therapeutic effects of UDCA on cholestatic liver diseases include: 1) protection of injured cholangiocytes against toxic effects of bile acids, 2) stimulation of impaired biliary secretion, 3) protection of hepatocytes against bile acid-induced apoptosis, 4) immunomodulatory properties with reduce immune-related liver damage [12-15].

In current literature, there are no a randomized, controlled trials testing the effect of UDCA in liver functional restoration of patients with obstructive jaundice after endoscopic treatment.

### Hypothesis

The hypothesis of this trial is that patients with obstructive jaundice, in which will be administered UDCA, in the early phase after endoscopic intervention will have better and faster functional restoration of the liver than patients in the control group.

### Aim and purpose of the research

#### General aim

The aim of this study is to evaluate the effect of UDCA in liver functional restoration of patients with obstructive jaundice in the early period after endoscopic intervention.

### Specific aims

Specific aims are:

– To evaluate the effect of UDCA in relation to the aetiology of obstructive jaundice.

– To assess that in which functional parameters of the liver, treatment with UDCA will have greater impact.

## Methods/Design

### Study objectives

This trial will be a prospective, open-label, randomized, and controlled study. The objective will be to evaluate the effect of ursodeoxycholic acid (UDCA) in the functional restoration of the liver in patients with obstructive jaundice in the early post-endoscopic phase.

### Study design

After diagnosis, patients with obstructive jaundice will be divided into two groups: (A) the test group in which will be administered UDCA in the early phase after endoscopic treatment, and (B) control group, in which no treatment will be applied with UDCA.

Diagnostic methods will be biochemical findings, ultrasound examination, endoscopic retrograde cholangio pancreatography (ERCP), CT-scan and magnetic resonance cholangio pancreatography (MRCP).

Serum-testing in patients with obstructive jaundice will include determination of bilirubin (total and direct fractions), alanine transaminase (ALT), aspartate transaminase (AST), gama-glutamil transpeptidase (GGT), alkaline phosphatase, albumin, and cholesterol levels. These parameters will be determined one day prior endoscopic intervention, and on the third, fifth, seventh, tenth, twelfth and fourteenth days after endoscopic intervention.

Endoscope procedure that will end with the internal derivation of bile shall be named as the internal bile drainage.

### Inclusion criteria are

– Patients with obstructive jaundice

– Serum bilirubin level higher than 50 μmol/l

– 19+ years of age

– Written informed consent

### Exclusion criteria are

Cholangitis

– Acute pancreatitis

– Pregnant women

– Women during the breastfeeding

– Suspected or proven primary liver diseases

– My family members

– Patients who are unable to understand our study purpose

During our trial, from the study will be excluded patients who show signs of serious side effects and allergic reactions after treatment with UDCA.

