### UDCA administration

UDCA administration will begin twenty-four hours after endoscopic procedure and will last fourteen days. UDCA dose will be administered at 750 mg/day, divided into three doses.

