### Power of the study

A clinically relevant improvement of liver functional tests is defined as an improvement of 70% of liver functional tests in test group, and an improvement only 40% in control group. In our study, to have an 80% chance of detecting about a 40% difference (70% vs. 40%) between two groups on improvement of liver functional tests at an alpha level of 0.05, the power calculation indicates that each of the two groups should have at least 48 patients.

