### Outcomes

The primary outcome measure in this trial is liver functional restoration. The secondary outcome is assessment liver functional parameters in which, treatment with UDCA, will have greater impact. Follow-up measures will be collected one day prior endoscopic intervention, and on the third, fifth, seventh, tenth, twelfth and fourteenth days after endoscopic intervention.

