### Randomisation

Patients have to sign an informed consent for the involving in the trial a day before endoscopic procedure. Randomisation will be performed at the time of transfer to the endoscope room by using random number generator at http://www.stattrek.com.

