### Data collection and statistical analyses

Data including serum-test results will be collected in a computer secured study platform. These data will be collected continuously, for each patient, starting one day before endoscopic procedure until the last data fourteen days after intervention.

X^2^-analysis or Fisher exact test will perform to test the differences in proportions of qualitative variables between groups. Mann Whitney U test and Kruskal Wallis test will use for testing the difference between quantitative variables when distribution is not normal and Student t-test or ANOVA test when distribution is normal. The level P < 0.05 will consider as the cut-off value for significance.

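### Removing patients from the study for reactions to UDCA is a one-arm exclusion after randomisation; it breaks the randomised comparison and can bias it, probably towards UDCA

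*Protocol article*

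**What the plan says.** The relevant statements are all in the Methods/Design part of the Protocol article.

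- Exclusion criteria: "During our trial, from the study will be excluded patients who show signs of serious side effects and allergic reactions after treatment with UDCA". The removal is from the study. Nothing says that only the drug is stopped while follow-up goes on.
- Randomisation: "Randomisation will be performed at the time of transfer to the endoscope room".
- UDCA administration: "UDCA administration will begin twenty-four hours after endoscopic procedure and will last fourteen days".
- Study design: group B is the "control group, in which no treatment will be applied with UDCA".
- Study objectives: "This trial will be a prospective, open-label, randomized, and controlled study".
- Outcomes: after the baseline sample, measurements are taken "on the third, fifth, seventh, tenth, twelfth and fourteenth days after endoscopic intervention".

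The section on data collection and statistical analyses names the tests to be used. It does not say that patients removed under this rule are followed up or analysed in the group to which they were randomised.

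**The concern.** The trigger is a reaction after treatment with UDCA, so it cannot occur in a patient who never receives UDCA. A control patient with a comparable event in the same days stays in the study. The two arms start as randomised groups, but one of them is then filtered by something that happens after randomisation and the other is not.

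Three features make this more than a formality. The removal can come before some or all of the outcome tests have been taken. The trial is open-label, and whether signs amount to a serious side effect is a judgement made with the arm known. And if blood tests stop when a patient leaves the study, no later analysis can recover the missing values or check which way the removal has moved the result.

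At stake are the validity of the between-arm comparison and the follow-up of the very patients who reacted to the test drug.

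**Working it through.** **1. Can the rule act in both arms?** The order of events is randomisation (on transfer to the endoscopy room), procedure, then UDCA from 24 hours later for 14 days in group A only. Every exclusion under the rule therefore follows randomisation and falls in group A. This step needs no assumption.

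**2. The plan's own sample size.** Inputs from the power section are "an improvement of 70% of liver functional tests in test group, and an improvement only 40% in control group", alpha 0.05, power 80% and at least 48 per group. The alpha is taken as two-sided, which the document does not state.

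- Uncorrected: n = [1.960·√(2·0.55·0.45) + 0.842·√(0.70·0.30 + 0.40·0.60)]² / 0.30² = 1.9435² / 0.09 = 42.0 per group.
- With continuity correction: (42.0/4)·[1 + √(1 + 4/(42.0·0.30))]² = 48.4, rounded up to 49.

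The stated 48 is reproduced to within one patient. The point does not depend on it, but 48 per group is used below.

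**3. Size of the bias when UDCA has no effect.** The true response is set at 40% in both arms, the plan's control figure. A fraction q of the UDCA arm is removed, and a fraction r of those removed would have responded. Both q and r are assumptions, because the document gives neither. The response rate among the UDCA patients kept is

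(0.40 − q·r) / (1 − q).

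For example, with q = 0.10 and r = 0 it is 0.40/0.90 = 44.4%, an apparent gain of 4.4 points. With q = 0.10 and r = 0.20 it is 0.38/0.90 = 42.2%, a gain of 2.2 points.

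The false-positive rate is the exact binomial probability that the two-sided uncorrected chi-square test rejects at 0.05. It compares 46, 43 or 41 UDCA patients (q = 5%, 10%, 15%) with 48 controls. With no removal it is 4.9%.

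| Would have responded (r) | Removed (q) | Apparent UDCA rate | Spurious difference | Two-sided false-positive rate |
|---|---|---|---|---|
| 0% | 5% | 42.1% | +2.1 points | 5.4% |
| 0% | 10% | 44.4% | +4.4 points | 6.7% |
| 0% | 15% | 47.1% | +7.1 points | 9.9% |
| 20% | 5% | 41.1% | +1.1 points | 5.0% |
| 20% | 10% | 42.2% | +2.2 points | 5.1% |
| 20% | 15% | 43.5% | +3.5 points | 6.0% |
| 40% | 5% to 15% | 40.0% | 0 | about 5% |

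The two-sided totals partly hide the shift. With r = 0, false positives in favour of UDCA rise from 2.5% to 4.0%, 5.8% and 9.5%. If the removed patients would have done better than the rest, the sign reverses: with r = 60% and q = 10%, the rate is (0.40 − 0.06)/0.90 = 37.8%, or 2.2 points against UDCA.

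**4. What keeping these patients does to power.** Suppose a fraction q of the UDCA arm reacts and does not improve, while 70% of the others improve. The UDCA rate over all randomised patients is 0.70·(1 − q), which is 66.5% at q = 5% and 63.0% at q = 10%. Power at 48 per arm with the uncorrected test is then about 75% and 62%, against 85% with no such patients.

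**The case against.** The strongest reply is that the direction of the bias is not shown. The rule acts on side effects and allergic reactions, whereas the outcome is liver function. Nothing in the document says that a patient with an allergic reaction recovers worse biochemically. This stands. A reader might infer that the rule necessarily inflates the benefit of UDCA, but the table shows no bias when removed patients would have responded like the others, and a bias against UDCA when they would have responded better.

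The larger figures are also a worst case. The 9.9% needs 15% removals, no responders among them and an uncorrected test. A continuity-corrected chi-square gives 3.3%, 4.3% and 6.8% in the r = 0 rows, against 2.9% with no removal, and the article does not say which form will be used. If reactions are rare, the effect is small. This too stands.

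A reader might also see a contradiction with the data collection section: "These data will be collected continuously, for each patient, starting one day before endoscopic procedure until the last data fourteen days after intervention". That is a general description of data flow, and the exclusion sentence can be read as a stated exception to it, so the two do not clearly conflict. Likewise, a reader might infer that the harmed patients vanish from the safety results. The rule does not forbid counting and reporting their reactions; what it puts at risk is their follow-up afterwards.

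Finally, analysis populations are commonly left to the full protocol or SAP, which are not shown. That does not answer the point. The article does not merely omit an intention-to-treat statement: it fixes a removal from the study, and an analysis plan cannot restore tests that were never taken.

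**Conclusion.** The point holds in a limited form. As written, the rule is a post-randomisation exclusion that can occur in the UDCA arm only, before outcome collection is complete, in an open-label trial. That much follows from the text alone.

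The resulting bias is probably in favour of UDCA, on the condition that the removed patients would have recovered worse than those kept. Its size rests on two rates that the document does not give. For 5% to 15% removed it runs from zero to 7.1 points, with false-positive rates from about 5% to 9.9% under the uncorrected test. At the milder assumption (20% of those removed would have responded), the false-positive rate stays between 5.0% and 6.0%. The case for a change therefore rests mainly on the broken randomised comparison, whose effect cannot be checked once follow-up ends, and less on a large expected bias.

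**What to change.** Separate stopping UDCA from leaving the study. The sentence under the exclusion criteria could be replaced by wording such as:

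*Patients in whom UDCA is stopped remain in the study and continue the scheduled blood tests to day 14 unless they withdraw consent. In the primary analysis they are analysed in the group to which they were randomised. Serious side effects and allergic reactions are reported by arm.*

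An analysis that leaves these patients out may be kept as a sensitivity analysis. When and why UDCA is stopped remains a clinical decision, which this change does not touch.

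The blood tests are already scheduled, so the direct cost is a short change of text and the effort to keep following patients after a reaction. The estimate may be less favourable to UDCA, and power may fall if reactions are frequent: about 75% instead of 85% at 48 per arm in the 5% example above. The sample size section states no allowance for this. If the sponsor expects reactions at such a rate, the number of patients should be reconsidered at the same time.

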### UDCA administration

UDCA administration will begin twenty-four hours after endoscopic procedure and will last fourteen days. UDCA dose will be administered at 750 mg/day, divided into three doses.

### Power of the study

A clinically relevant improvement of liver functional tests is defined as an improvement of 70% of liver functional tests in test group, and an improvement only 40% in control group. In our study, to have an 80% chance of detecting about a 40% difference (70% vs. 40%) between two groups on improvement of liver functional tests at an alpha level of 0.05, the power calculation indicates that each of the two groups should have at least 48 patients.

### Data sources and search strategy

An electronic search was performed on PubMed (from 1 January 1985 to 1 February 2012). A combination of keywords and MeSH terms where: ‘ursodeoxycholic acid’ AND ‘obstructive jaundice’, ‘obstructive jaundice’ AND ‘liver function tests’, ‘obstructive jaundice’ AND ‘acute renal failure’. I have used, also, limits: Type of article (selection was- clinical trial, meta-analyses), Species (selection was- human, animals), Text options (selection was- links to free full text, abstract), Languages (English), Sex (male, female), Age (all adult 19+ years), Field (all fields).

### Outcomes

The primary outcome measure in this trial is liver functional restoration. The secondary outcome is assessment liver functional parameters in which, treatment with UDCA, will have greater impact. Follow-up measures will be collected one day prior endoscopic intervention, and on the third, fifth, seventh, tenth, twelfth and fourteenth days after endoscopic intervention.

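### The primary outcome has no marker, visit or patient-level criterion, so the proportion behind the sample size cannot be computed and any of up to 48 comparisons could be presented as primary

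*Protocol article*

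**What the plan says.** The Outcomes section gives the primary outcome in one sentence, "The primary outcome measure in this trial is liver functional restoration", followed by a secondary outcome drawn from the same measurements: "The secondary outcome is assessment liver functional parameters in which, treatment with UDCA, will have greater impact".

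Under Study design, the laboratory panel is "determination of bilirubin (total and direct fractions), alanine transaminase (ALT), aspartate transaminase (AST), gama-glutamil transpeptidase (GGT), alkaline phosphatase, albumin, and cholesterol levels". That is eight values if total and direct bilirubin count separately. The abstract lists bilirubin once, which gives seven. Apart from the sample taken the day before the procedure, the values are measured "on the third, fifth, seventh, tenth, twelfth and fourteenth days after endoscopic intervention".

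Power of the study offers the only definition of improvement: "A clinically relevant improvement of liver functional tests is defined as an improvement of 70% of liver functional tests in test group", set against "an improvement only 40% in control group". From these rates, with 80% power and alpha 0.05, it derives at least 48 patients per group.

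Data collection and statistical analyses lists chi-square or Fisher tests for proportions and parametric or rank tests for quantitative variables. It then gives one rule for all of them: "The level P < 0.05 will consider as the cut-off value for significance". No test is tied to a named outcome or visit.

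**The concern.** An endpoint definition has to say, for one patient and without reference to the arm, whether the outcome was reached. The power section instead defines improvement by the result expected in each group. Two analysts given the complete data could not be relied on to compute the same proportion improved, or to agree on whether the trial met its primary outcome.

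It is not even clear what the 70% and 40% are shares of. They could be shares of patients, shares of tests within a patient, or sizes of change in a value. Only the first fits a two-proportion sample size.

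Two things are at stake. The stated 80% power belongs to an endpoint that the Outcomes section does not contain. And nothing in the text prevents a favourable marker on a favourable day from being called liver functional restoration afterwards. The trial is open-label, so that choice could be made with knowledge of treatment and results.

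**Working it through.** **1. Reproduce the 48 per group.** Inputs from Power of the study: 0.70 and 0.40, power 0.80, alpha 0.05. Sidedness is not stated; two-sided is assumed.

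- Pooled normal formula: n = [1.960·√(2·0.55·0.45) + 0.842·√(0.70·0.30 + 0.40·0.60)]² / 0.30² = (1.379 + 0.565)² / 0.09 ≈ 42.0 per group.
- With continuity correction: (42.0/4)·[1 + √(1 + 4/(42.0·0.30))]² ≈ 48.4, which rounds up to 49.
- Exact two-sided Fisher test: power 78.6% at 47 per group and 80.05% at 48.

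So 48 is the Fisher result for a 30-point difference. The section's text calls the difference about 40%, but a 40-point difference would need only 23–29 per group. The figure therefore presupposes one binary outcome per patient, compared once at 0.05.

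**2. Look for that binary outcome.**

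- Outcomes: a label only, with no variable, day or threshold.
- Power of the study: two group rates, with no rule for classifying a patient.
- Statistical analyses: a test for proportions, but no named responder variable to apply it to.

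The powered proportion cannot be computed from the text.

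**3. Count what could stand in for it.** 8 values × 6 post-procedure visits = 48 comparisons (7 × 6 = 42 if bilirubin counts once).

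**4. Chance of at least one P < 0.05 with no true effect, if all are tested.** For independent tests:

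- 48 tests: 1 − 0.95⁴⁸ = 91.5%
- 42 tests: 1 − 0.95⁴² = 88.4%
- 8 tests at one visit: 1 − 0.95⁸ = 33.7%
- 48 tests, only results favouring UDCA: 1 − 0.975⁴⁸ = 70%

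The values are certainly correlated, but the documents give no correlations. The following are assumptions: simulated normal test statistics, the same correlation between all visits, 50,000 runs per setting.

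| Between markers | Between visits | Any of 48, two-sided | Any of 48 favouring UDCA | 8 markers, day 14 only |
|---|---|---|---|---|
| 0.3 | 0.7 | 71% | 39% | 30% |
| 0.5 | 0.7 | 63% | 33% | 25% |
| 0.7 | 0.9 | 36% | 18% | 19% |
| 0.9 | 0.95 | 20% | 10% | 12% |

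If correlation instead fades with time between visits, the first and last rows of the two-sided column become 78% and 23%.

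**5. What co-equal primary tests would cost.** With Bonferroni and the same 70% vs 40%:

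- 8 tests, 0.05/8 = 0.00625: 69 per group (76 with continuity correction); power at 48 per group about 59%.
- 48 tests, 0.05/48 = 0.00104: 92 per group (99 with correction); power at 48 per group about 37%.

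**The case against.** The best defence is that the article points to a single comparison. The power section uses one pair of proportions at one alpha, and the analysis section lists Fisher's test, which reproduces the 48. The visit lists are measurement schedules. Adjustment for multiple testing and the allocation of tests to visits are often left to an analysis plan, which is not shown here.

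Much of this stands, and it rules out three stronger readings that a reader might infer:

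- **That 48 tests are planned.** No section schedules them. The general cut-off permits them; it does not prescribe them.
- **That a false positive is more likely than not.** This holds for two-sided results at independence or moderate correlation. With high correlation, or with correlated tests counted only in favour of UDCA, most of the figures fall below 50%.
- **That the secondary outcome ranks markers by P value.** The text speaks only of where the treatment has more effect and gives no ranking rule.

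The defence does not reach the central point. If one responder comparison is intended, its criterion is what the article fails to supply. The article has an outcomes section and a power section; one gives a label and the other a circular definition. That is a definition stated badly, and an unseen analysis plan does not repair it.

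**Conclusion.** The point holds, and it must be fixed. That the primary outcome is undefined, and does not connect with the sample size, follows from the text alone and rests on no simulation.

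The error-rate part is conditional: it is what could happen if the general cut-off were applied across markers and visits and any result were allowed to count as primary. In that case the two-sided false-positive risk is 91% at independence. It is about 20–71% for assumed correlations of 0.3–0.9 between markers and 0.7–0.95, taken as equal, between visits. Counting only results in favour of UDCA, the correlated range is about 10–39%. Every one of these is well above the two-sided 5%, or the 2.5% in one direction, that a single test would carry. How far above cannot be settled from the documents.

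**What to change.** Before comparative results are looked at:

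- Name one binary primary endpoint per patient, applied identically in both arms: one marker or a defined composite, one visit, and one threshold of change from the pre-procedure value. A pre-set percentage fall in total bilirubin at day 14 would be one example.
- Compare it once, by Fisher or chi-square, at two-sided 0.05.
- State that 70% and 40% are the assumed responder rates for that endpoint. The 48 per group gives 80% power only if they apply to it; otherwise restate the power.
- Make all other markers and visits secondary, with Holm adjustment or with estimates and 95% confidence intervals only.
- Report which markers respond most as effect sizes on a common scale with confidence intervals, for example ratios of geometric means.

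The cost is a change of wording, with no new measurements. More patients would be needed only if the chosen endpoint does not support the assumed rates. There are two downsides. A result in another marker or on another day can no longer be called primary. And a single-day endpoint does not itself test the hypothesis of faster restoration, which would become secondary.

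### The secondary outcome asks which liver parameters UDCA affects more, but the only inference named is a separate test per variable at P < 0.05, which cannot answer that

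*Protocol article*

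**What the plan says.** In the protocol article, the Outcomes section gives one secondary outcome: "The secondary outcome is assessment liver functional parameters in which, treatment with UDCA, will have greater impact". The Specific aims section puts the same question: "To assess that in which functional parameters of the liver, treatment with UDCA will have greater impact".

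The Study design section lists the markers: "determination of bilirubin (total and direct fractions), alanine transaminase (ALT), aspartate transaminase (AST), gama-glutamil transpeptidase (GGT), alkaline phosphatase, albumin, and cholesterol levels". That is seven, or eight if total and direct bilirubin are counted separately.

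The section on data collection and statistical analyses names chi-square or Fisher tests for proportions, and Mann-Whitney, Kruskal-Wallis, t-test or ANOVA for quantitative variables. For proportions the comparison is explicitly between arms: "Fisher exact test will perform to test the differences in proportions of qualitative variables between groups". The section closes with one decision rule: "The level P < 0.05 will consider as the cut-off value for significance". It names no contrast between markers and no ranking by effect size.

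**The concern.** The question concerns the relative size of several treatment effects. The named tests each ask whether the groups differ on a single variable. A reader who wants to know where UDCA acts more is left with a list of P values, some below 0.05 and some above.

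Such a list does not answer the question, for two reasons. First, a P value mixes the size of an effect with the variability of the marker, so a modest effect on a stable marker can look stronger than a larger effect on a noisy one. Second, markers with identical true effects will often fall on opposite sides of 0.05 by chance. Raw differences do not help either: the markers are measured on different scales, and albumin improves by rising while the bilirubin fractions and enzymes improve by falling.

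At stake is a published statement that UDCA acts on some liver functions and not on others, when the split may be chance.

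**Working it through.** **Inputs from the article (Power of the study).** Significance level: "at an alpha level of 0.05", taken as two-sided because sidedness is not stated. Power and rates: "to have an 80% chance of detecting about a 40% difference (70% vs. 40%) between two groups". Sample size: "each of the two groups should have at least 48 patients".

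**Assumptions, not in the article.** All markers have the same true effect. Each per-marker test has the planned 80% power. The test statistics are normal, with a common correlation ρ between 0 and 0.9.

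**Step 1: reproduce the planned sample size.** With mean rate 0.55 and difference 0.30:

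n = [1.96·√(2·0.55·0.45) + 0.842·√(0.7·0.3 + 0.4·0.6)]² / 0.30² = 41.97, so 42 without continuity correction.

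With the correction: n = (41.97/4)·[1 + √(1 + 4/(41.97·0.30))]² = 48.4, so 49.

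Exact enumeration at 48 per group gives a Fisher exact power of 0.800 (uncorrected chi-square 0.854). The stated 48 is therefore reproduced, and 80% is a fair working value for a marker that has the design effect.

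**Step 2: two equally affected markers.** With per-test power p and z_p its normal quantile (0.842 for p = 0.80), counting significance in the expected direction:

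P(exactly one significant) = 2·[p − Φ₂(z_p, z_p; ρ)], which is 2p(1 − p) when ρ = 0.

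At p = 0.80 and ρ = 0 this is 2·0.80·0.20 = 0.32.

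| Power | ρ = 0 | 0.3 | 0.5 | 0.7 | 0.9 |
|---|---|---|---|---|---|
| 80% (planned) | 32% | 27% | 23% | 17% | 10% |
| 50% (sensitivity) | 50% | 40% | 33% | 25% | 14% |
| 90% (sensitivity) | 18% | 16% | 14% | 11% | 6% |

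**Step 3: all markers equally affected, mixed verdict (some significant, some not).** Equicorrelated normal simulation, 200,000 runs per setting, power 80%:

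| Markers | ρ = 0 | 0.3 | 0.5 | 0.7 | 0.9 |
|---|---|---|---|---|---|
| 8 | 83% | 67% | 57% | 44% | 25% |
| 7 | 79% | 64% | 54% | 42% | 24% |

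Check at ρ = 0 with eight markers: 1 − 0.8⁸ − 0.2⁸ = 0.832, which agrees.

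**Step 4: what a direct contrast can do.** A direct test of the difference between two effects calls equally affected markers different 5% of the time by design. For its power, let one marker have the standardised effect that gives 80% power, (1.96 + 0.842)/√(48/2) = 0.57 SD, and the other none:

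power = Φ(2.80/√(2(1 − ρ)) − 1.96)

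This gives about 51%, 66%, 80% and 95% for ρ = 0, 0.3, 0.5 and 0.7. The formula is on a standardised scale. On the log-ratio scale it is a guide only, because the markers' variances will differ.

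**The case against.** The strongest reply is that the article never commits the error. A reader might infer that greater impact will be awarded to whichever markers cross P < 0.05. No sentence says this: the test list and the cut-off are general, and neither is tied to the secondary outcome. An unseen analysis plan could contain a contrast. This stands as a limit on the claim. What remains is a mismatch between the stated question and the stated inference: adding detail to the named tests would not turn them into a comparison between markers.

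The secondary outcome could also be read as greater impact than in the control group, in which case per-marker tests between arms would address it. That reading is possible but less natural, because both statements of the aim ask in which parameters the impact is greater.

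The wording of the statistical section is loose. Kruskal-Wallis and ANOVA are not needed for two arms and may serve the aetiology aim. This does not supply a comparison between markers.

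The power section speaks of improvement, so each marker might be scored as improved or not, which is free of units and handles direction. The article does not say that this is done marker by marker, and a test of each proportion would still leave significant set against non-significant.

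The rates in the working depend on assumptions. This is fair. For a pair at 80% power the rate falls to 10% at ρ = 0.9. Treating total and direct bilirubin as exchangeable with the other markers is a simplification, since one is a component of the other.

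**Conclusion.** The concern holds as a mismatch between question and method. The secondary outcome compares effects across markers, and the named inference gives no valid basis for that comparison.

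At the planned 80% power, a pair of equally affected markers splits in about 17% to 32% of trials (ρ from 0.7 to 0), and eight such markers give a mixed verdict in about 44% to 67% (ρ from 0.7 to 0.3). These figures assume equal true effects, the planned power for every marker, and correlations that the article does not give.

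A reader might quote a mixed-verdict rate near 90% for eight markers. That figure (0.895 at ρ = 0.3) requires 50% power per marker, whereas the only power the article states is 80%, so it should not be presented as the plan's own risk.

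The point affects the interpretation of a secondary outcome and should be corrected. It does not touch the primary comparison.

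**What to change.** State the following for the secondary outcome.

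1. For each marker, estimate the baseline-adjusted UDCA versus control ratio of geometric means at day 14, the last scheduled measurement. Align the sign of the log-ratio so that improvement is positive: reverse it for markers that improve by falling and leave it for albumin.
2. Show all markers with 95% confidence intervals in one display, and describe relative impact from these estimates, not from P values.
3. State that one marker responds more than another only if a confidence interval for the difference of their aligned log-ratios excludes zero. Obtain it by a patient-level bootstrap or a joint model, so that the correlation between markers in the same patient is respected.
4. A display in standardised units may be added as a sensitivity analysis, with a note that it depends on each marker's variability and so shares part of the weakness of P values.

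The cost is a little more analysis work, with no new patients, visits or measurements. Claims will be more cautious, because contrasts between markers have only moderate power at 48 per group unless the markers are strongly correlated.
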